### Sample size calculation

The RCT study, in which the present research is embedded, is powered to detect a 15% difference in provided personalized lifestyle advice by including 900 patients clustered within 30 practices [30]. For the present research, we calculated the sample size for detecting a 15% difference in response rate of patients who are approached by 1) an invitation for participation in this study with a telephone interview) and 2) the choice for participating by a telephone interview or a paper-based test. Assuming alpha is 0.05, power of 0.80, a response rate of 50% in the first group and 65% in the second group, we estimated that we need to include 338 patients.

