### Sample

The sample will consist of health care professionals, patients with high risk for CVD or established CVD and their alters.

#### **
*Health care professionals*
**

We will include all health care professionals working in general practices participating in the RCT and who are involved in patient care (typically, general practitioners, practice nurses, and practice assistants). Based on power calculations in the RCT, 30 practices are planned to be included.

#### **
*Patients*
**

Eligible patients are adults aged 18 or older, with high risk of CVD or established CVD and who are capable of providing informed consent [30]. Patients with high risk for CVD have a risk score of 20% or higher of 10-years-morbidity and mortality due to CVD. International Classification of Primary care (ICPC) codes will be used to extract eligible patients from medical records. Exclusion criteria are: diabetes mellitus, pregnancy and lactation, terminal illness, cognitive impairments, and poor language skills. Per practice we plan to include 15 patients with established CVD and 15 at high risk.

#### **
*Alters*
**

*Alters of health care professionals* will comprise individuals with whom information on CVRM is exchanged but who are not part of the general practices’ network, as well as opinion leaders from outside general practices. We aim to include all alters of health care professionals.

*Alters of patients* include key individuals for information exchange, which most likely will be spouses or children of patients. We aim to include up to four persons considered to be important for dealing with patients’ condition or disease as indicated by the included patients in our measurements.

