Patients will be selected from the general practices’ electronic data base using ICPC codes during practice visits of the RCT. They will receive a questionnaire booklet at the start and end of the intervention period on behalf of the RCT [30]. For inclusion in the network study, we will include three basic network questions (see Additional file 1) in this questionnaire booklet followed by an invitation for participation in the network study. An informed consent form will be enclosed and will be returned along with the questionnaire booklet of the RCT. During the inclusion of the first six practices, patients will be randomized into one of two groups. The first group will receive an invitation in the questionnaire booklet to participate in the network study by a telephone interview. The second group will be invited by the choice to participate by 1) a telephone interview *or* 2) a paper-based questionnaire. After inclusion of these practices we will invert the design for another six practices so that the first group will receive an invitation to participate in the network study by a paper-based questionnaire and the second group will be invited by providing the choice to participate by either 1) a paper-based questionnaire or 2) a telephone interview. These response groups are included so that we will be able to compare which approach is most feasible for including patients in network measurements as current research on this is scarce. For inclusion of patients from additional practices, we will employ the inclusion method as assessed to be most feasible. The basic questions are incorporated in the RCT questionnaire to ensure that basic data for all patients is included. Questionnaires will be send and interviews will be held approximately two weeks after receipt of accepted invitations.

#### **
*Alters of patients*
**

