### Statistical analyses

Response rates for health professionals and patients will be determined. For patients we will compare response rates between the patient group invited by either a single option for participation and the group that will be offered the choice to participate by either a telephone interview or a paper-based test in order to assess which method is most feasible for including them in social network research using *X*^2^ tests.

Reliability of reported social network connections will be investigated by examining the proportion of all possible connections that will be mutually reported present or absent (reciprocity coefficients in non-directed networks). In accordance with guidelines on handling missing values, we will substitute these by values as provided by responses of other individuals. In case of no information on connections, we will indicate no contact by a filling in a zero in the data [41].

For describing social networks of health professionals and patients we will compute network parameters and provide visualization by using graphic displays. Random permutation tests will be used for comparisons of network characteristics.

For testing our hypotheses and further explorative analyses, controlling for potential confounders, we will use multivariate logistic regression models to investigate the effect of social networks characteristics on professional performance of practice nurses and patients’ self-management and health outcomes.

In the analysis of professional performance of practice nurses regression models will include six network characteristics (density, frequency of contact, homogeneity, presence of informal opinion leaders and CVRM-coordinators, and centrality) as predictors of main interest. As control variables we will include trial arm (intervention vs control group), personal characteristics (amongst others education, years of experience in profession), and practice characteristics (practice size, involvement in other projects or organizations).

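### The 338 patients and 80% power are stated for telephone-only versus choice, but the design randomises that contrast in only six of the twelve practices; the figure fits only single option versus choice over all twelve

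*Protocol article*

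**What the plan says.** The protocol article describes the invitation experiment in four places.

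- **Sample size calculation.** The contrast sized is "an invitation for participation in this study with a telephone interview) and 2) the choice for participating by a telephone interview" or on paper. The error rates are given as "Assuming alpha is 0.05, power of 0.80". The assumed response rates and the resulting total are then stated together: "a response rate of 50% in the first group and 65% in the second group, we estimated that we need to include 338 patients".
- **Recruitment process and data collection, Patients.** In the first six practices patients are randomised between a telephone-only invitation and a choice. Then: "After inclusion of these practices we will invert the design for another six practices". In that second block the single option is a paper questionnaire, again against a choice. All further practices receive whichever method is judged most feasible.
- **Sample, Patients.** "Per practice we plan to include 15 patients with established CVD and 15 at high risk", so 30 per practice.
- **Primary outcomes for patients (Response rates) and Statistical analyses.** The outcome is one option versus two options, without naming the mode of the single option. The analysis section plans chi-square tests of the same contrast, with the second group having both modes open to it: "we will compare response rates between the patient group invited by either a single option for participation and the group that will be offered the" …

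**The concern.** Three things should match and do not: the contrast that was powered (telephone-only versus choice), the allocation (half of the randomised practices have telephone-only, half paper-only), and the contrast described for analysis (any single option versus choice).

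This matters because response rate is a declared main outcome for patients, is the subject of research aim 4, and is the only outcome for which this study gives its own sample size. It also decides how patients in the remaining 30 − 12 = 18 practices are invited. Three methods are candidates for that rollout: telephone-only, paper-only and choice. A result averaged over two kinds of single option does not show whether choice beats either one, and the stated power may not apply to the contrast it is attached to.

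**Working it through.** **Inputs.** From the sample size section: p1 = 0.50, p2 = 0.65, alpha 0.05, power 0.80. From the sample section: 15 + 15 = 30 patients per practice. From the recruitment section: six practices per block, two blocks. Assumed here because the article does not say: two-sided test, 1:1 allocation, and 30 patients randomised per practice.

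**Step 1: reproduce 338.** With p̄ = (0.50 + 0.65)/2 = 0.575,

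n per group = [1.960·√(2·0.575·0.425) + 0.842·√(0.50·0.50 + 0.65·0.35)]² / 0.15²
= [1.960·0.6991 + 0.842·0.6910]² / 0.0225
= (1.3702 + 0.5816)² / 0.0225 = 3.8095 / 0.0225 = 169.3.

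Twice 169 is 338. The figure is sound for two groups of 169 (power 79.9%). A one-sided test would give 268 in total and a continuity correction 366, so a two-sided uncorrected calculation was evidently used.

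**Step 2: the named contrast as allocated.** 6 × 30 = 180 patients, 90 per group. Power is Φ(z), where

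z = [0.15·√n − 1.960·0.6991] / 0.6910.

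At n = 90: z = (1.4230 − 1.3702)/0.6910 = 0.076, power 53%. The 95% confidence interval half-width is 1.960·√((0.25 + 0.2275)/90) = 0.143, about 14 points. From a 50% base, the difference detectable with 80% power is about 20 points.

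**Step 3: sensitivity to the number invited.** Six practices, same formula:

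| Invited per practice | Per group | Power, 50% vs 65% |
|---|---|---|
| 30 | 90 | 53% |
| 40 | 120 | 65% |
| 50 | 150 | 75% |
| 56 | 168 | 80% |
| 60 | 180 | 82% |

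Reaching 338 in six practices needs 338/6 = 56.3 patients each. At 30 per practice it needs 338/30 = 11.3, that is twelve practices.

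**Step 4: single option versus choice over twelve practices.** 12 × 30 = 360 patients, 180 per group. The single-option rate is then the average of the telephone-only and paper-only rates. Holding telephone-only at 50% and choice at 65%, with an assumed range for paper-only because the article gives no figure:

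| Paper-only rate | Single-option average | Difference from choice | Power |
|---|---|---|---|
| 50% | 50.0% | 15.0 points | 82% |
| 55% | 52.5% | 12.5 points | 67% |
| 60% | 55.0% | 10.0 points | 49% |
| 65% | 57.5% | 7.5 points | 31% |

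So the 338 is covered at the planned practice size only by the twelve-practice contrast, under an equal-rate assumption that the article does not state.

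**The case against.** The strongest reply is that the authors meant single option versus choice all along. The outcome definition and the analysis section both describe it that way, and 360 exceeds 338. This is probably right, and the fix adopts it. It does not rescue the sample size section, which names telephone-only and gives no paper-only rate.

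A second reply is that 53% is not fixed by the documents. The 30 per practice is an inclusion target, whereas a response rate is counted over patients invited. The invitation travels in the RCT questionnaire booklet, the article does not say how many booklets each practice sends, and it refers to the RCT protocol for the inclusion procedure. If 30 were the number responding at 50% to 65%, about 46 to 60 would be invited and power would be roughly 71% to 82%. This stands: 53% is conditional. A reader might infer that the telephone comparison is certainly underpowered, and the documents do not support that.

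Third, the analysis section speaks of chi-square tests in the plural and never says outright that the two blocks are merged. Merging is the natural reading, not a stated rule. If separate tests were intended, each would have one block's patients and the 80% would not carry over at 30 per practice.

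Fourth, a reader might infer that merging biases the result. With 1:1 randomisation within each block it does not confound option with block. The lower power in Step 4 reflects a smaller true average difference; the loss is in interpretation. Nor does the plan claim a randomised comparison of telephone-only with paper-only, or say that the rollout would rest on one.

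**Conclusion.** The point holds as a mismatch between the contrast sized, the allocation and the contrast to be tested. The 338 is correct arithmetic attached to the wrong description. If 30 patients per practice are randomised 1:1, telephone-only versus choice has about 53% power rather than 80%. The 80% is met at that practice size only for single option versus choice over twelve practices (82%), and only if paper-only response is also 50%.

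This should be fixed, but it does not threaten the study. It affects one main patient outcome and the choice of invitation method for the later practices. The network hypotheses are unaffected.

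**What to change.** 1. **Sample size calculation.** State that 338 refers to single option versus choice pooled over the twelve randomised practices, and that it assumes the same 50% response to telephone-only and paper-only invitations. Give the number of patients invited per practice and the resulting power of each six-practice contrast at the assumed rates (about 53% if 30 are invited).
2. **Statistical analyses.** Report telephone-only versus choice and paper-only versus choice separately, each with a confidence interval. State that the pooled comparison is stratified by block or by practice, for example with a Mantel-Haenszel test.
3. **Rollout.** Say that the method for the remaining practices will be chosen from the randomised differences within each block, not from telephone-only against paper-only across blocks.

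The cost is a few sentences, slightly more analysis and a less favourable stated power for the separate contrasts. No extra patients are needed.

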### Data analysis

We will use UCINET for constructing and obtaining social network parameters of general practices on broad and specific information exchange and general information receipt networks of patients. The statistical package R will be used for all other analyses. All data analyses will be based on ‘intention to treat’.

### Construction of network characteristics

*Density* represents the proportion of all possible connections in a network that are actually present. *Homogeneity* represents the similarity of persons within clusters. Similarity of persons will be assessed regarding priority given to preventive treatment and CVRM targets, and other individual characteristics. *Centrality* is a measure for the extent to which a network is organized around a single person and can be divided into in- and outdegree centralization. The first specifies information flow from various network members to a single person, the latter whether information flows from a single person to the other network members.

### Statistical analyses

Response rates for health professionals and patients will be determined. For patients we will compare response rates between the patient group invited by either a single option for participation and the group that will be offered the choice to participate by either a telephone interview or a paper-based test in order to assess which method is most feasible for including them in social network research using *X*^2^ tests.

Reliability of reported social network connections will be investigated by examining the proportion of all possible connections that will be mutually reported present or absent (reciprocity coefficients in non-directed networks). In accordance with guidelines on handling missing values, we will substitute these by values as provided by responses of other individuals. In case of no information on connections, we will indicate no contact by a filling in a zero in the data [41].

For describing social networks of health professionals and patients we will compute network parameters and provide visualization by using graphic displays. Random permutation tests will be used for comparisons of network characteristics.

For testing our hypotheses and further explorative analyses, controlling for potential confounders, we will use multivariate logistic regression models to investigate the effect of social networks characteristics on professional performance of practice nurses and patients’ self-management and health outcomes.

In the analysis of professional performance of practice nurses regression models will include six network characteristics (density, frequency of contact, homogeneity, presence of informal opinion leaders and CVRM-coordinators, and centrality) as predictors of main interest. As control variables we will include trial arm (intervention vs control group), personal characteristics (amongst others education, years of experience in profession), and practice characteristics (practice size, involvement in other projects or organizations).

In the analyses of self-management and health outcomes in patients, several multivariate logistic regression models will be estimated. For self-management, separate models will be estimated on physical activity, diet, and smoking. For health outcomes, separate models will be estimated on SBP, cholesterol, and risk score. Models will include four network characteristics as predictors: number of alters with favorable health behaviors, who are also connected among each other, number of alters with depressive symptoms, and number of alters who can provide CVRM-related information. The regression models will be controlled for trial arm (intervention vs control group), patient group (high risk or established CVD), and several personal characteristics: age, sex, ethnicity, marital status, SES, patient activation, therapy adherence, and depressive symptoms.

Two approaches will be used to investigate effects of social network characteristics on change in professional performance of practice nurses and self-management and health outcomes of patients after the intervention period at six month follow-up. First, follow-up outcomes measures will be treated as dependent variables. We will estimate similar models as described above and include baseline measures of outcomes of interest as predictors. Second, we will consider change as the difference between the baseline- and follow-up measures of the diverse outcomes of interest. Ordinal logistic regression models will be estimated, with change represented in three categories; a shift from inadequate to adequate outcomes, no change, and shift from adequate to inadequate outcomes.

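### The single-option versus choice invitation comparison is planned as an ordinary chi-square test that ignores practice and phase; a practice-stratified test would gain a little power at no cost

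*Protocol article*

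**What the plan says.** Under Recruitment process and data collection (Patients), the randomisation is described in two steps. In the first step, "During the inclusion of the first six practices, patients will be randomized into one of two groups": telephone interview only, or a choice of telephone or paper. Then: "After inclusion of these practices we will invert the design for another six practices", where the contrast is paper only versus a choice. The stated purpose is: "These response groups are included so that we will be able to compare which approach is most feasible". Practices recruited after these twelve receive the preferred method: "For inclusion of patients from additional practices, we will employ the inclusion method as assessed to be most feasible".

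Under Statistical analyses, the plan is to "compare response rates between the patient group invited by either a single option for participation and the group that will be offered the choice", in order to assess "which method is most feasible for including them in social network research using" chi-square tests. No stratification or adjustment is named for this comparison. The regression models in the same section, by contrast, list control variables.

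Under Sample size calculation, the inputs are "Assuming alpha is 0.05, power of 0.80, a response rate of 50% in the first group and 65% in the second group", and "we estimated that we need to include 338 patients". No practice term enters. The section on primary outcomes for patients lists response rates among the main outcomes, and the fourth research aim is to evaluate methods of including patients.

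**The concern.** Willingness to take part in a network interview or questionnaire may well differ between practices. It may also differ between the first and second six practices, which use different single-option modes. When individual patients are randomised across practices, that variation can be removed from the comparison by comparing like with like inside each practice. An ordinary chi-square test on the combined patients leaves it in the error term. What is at stake is precision on a main outcome whose result also determines how the remaining practices are invited. The validity of the test is not at stake.

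**Working it through.** **Inputs.** From the article: response 50% versus 65%, alpha 0.05, power 0.80, total 338 (Sample size calculation); 15 + 15 = 30 patients per practice and 30 practices (Sample); 6 + 6 = 12 practices with randomised invitations (Recruitment process and data collection). Assumed because not given: 1:1 allocation, two-sided alpha, balance within practice, full recruitment of 30 per practice, and the size of the between-practice variation.

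**Step 1: reproduce 338.** The usual two-proportion formula, without continuity correction and with mean proportion 0.575, is

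n per group = [1.96 × √(2 × 0.575 × 0.425) + 0.842 × √(0.50 × 0.50 + 0.65 × 0.35)]² / 0.15² = [1.96 × 0.699 + 0.842 × 0.691]² / 0.0225 ≈ 169.3.

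Rounded to 169 per group this is 338 in total; rounded up to 170 it is 340. The stated figure is therefore the sample size for an unstratified two-group comparison.

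**Step 2: which patients it needs.** Six practices give 6 × 30 = 180 patients, and twelve give 12 × 30 = 360. The 338 is reached only by combining the two phases, so a combined analysis is the natural reading. With 180 per group, the power by the same formula is 0.82.

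**Step 3: approximate gain from stratifying.** With balanced individual randomisation within practices, stratification multiplies the variance of the difference by about (1 − ICC). The equivalent sample size is 338 × (1 − ICC), rounded up: 335 at ICC 0.01, 322 at 0.05, 305 at 0.10 and 271 at 0.20. Stratifying does not raise the required number.

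**Step 4: simulation at the planned size.** Twelve practices with 14 + 14 patients each (336 in total), 40,000 runs, overall rates held at 50% and 65% (57.5% in both groups for type I error), ordinary chi-square versus Cochran-Mantel-Haenszel (CMH) by practice:

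| Assumed ICC | Power, chi-square | Power, CMH | Type I error, chi-square | Type I error, CMH |
|---|---|---|---|---|
| 0.01 | 0.809 | 0.808 | 0.051 | 0.051 |
| 0.05 | 0.811 | 0.816 | 0.045 | 0.047 |
| 0.10 | 0.817 | 0.836 | 0.043 | 0.051 |
| 0.20 | 0.829 | 0.874 | 0.034 | 0.052 |

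The power differences are about 0, 0.5, 2 and 4.5 points.

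**Step 5: second simulation, different parameterisation.** Twelve practices of 30, balanced within practice, with practice effects of standard deviation 0.4, 0.6 and 0.9 on the logit scale. Power for chi-square versus CMH is 0.80 v 0.81, 0.78 v 0.80 and 0.71 v 0.76. Chi-square type I error is 0.048, 0.044 and 0.035, against about 0.05 for CMH. The absolute power falls for both tests as the variation grows. That is expected when 50% and 65% describe an average practice, because the overall difference then shrinks below 15 points. The relevant figure is the gap between the tests: about 1, 2 and 5 points.

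**The case against.** The strongest reply is that nothing here is wrong. In Step 4 the chi-square test keeps at least the planned 0.80 power throughout, and its type I error does not materially exceed 5%. With little between-practice variation the stratified test gains nothing. Neither 1:1 allocation nor balance within practice is stated, and the conservatism depends on that balance. The article speaks of tests in the plural, so a separate test per phase is possible. An article may also leave stratification to a fuller document. Most of this stands, and it limits the point to an efficiency gain. It does not remove the point: the article does name a test, that test has no practice term, and the reply gives no reason to prefer it.

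Two stronger readings are tempting, and neither is supported.

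- A reader might infer that ignoring practice makes the test anti-conservative, as it would in a cluster-randomised comparison. Here individual patients are randomised, and under balance the effect runs the other way.
- A reader might infer that patients from later practices, if all were offered the choice, would join that group without concurrent controls and bias the result. The article does not plan this. The later method is chosen from the comparison, so later practices cannot be part of the test that selects it. The comparison is also sized at 338, close to the 360 in the twelve practices and far from the 30 × 30 = 900 of the whole study. Error rates calculated for that scenario say nothing about the plan as written.

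**Conclusion.** The planned chi-square test is valid but does not use the structure of the design. If allocation is balanced within practice, it is mildly conservative. It loses about 1 point of power or less at low between-practice variation (ICC up to 0.05, or logit standard deviation 0.4). The loss is about 2 to 5 points at moderate to high variation (ICC 0.10 to 0.20, or logit standard deviation 0.6 to 0.9). These sizes rest on an assumed range of variation, 1:1 allocation and full recruitment of the twelve practices. No conclusion of the study is shown to be at risk. This is a small improvement worth making because it is free, and it concerns one of the main outcomes.

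**What to change.** In Statistical analyses, replace the chi-square comparison of response rates with a Cochran-Mantel-Haenszel test stratified by practice, or logistic regression conditional on practice. Because each practice belongs to one phase only, stratifying by practice also stratifies by phase. Report the stratified risk difference (choice minus single option) with its 95% confidence interval.

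Add that the analysis covers the 12 practices with randomised invitations and that response in later practices is described only. This makes explicit what the text already implies.

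The cost is a sentence or two in the analysis section. No new data are needed, because practice is known for every patient, and the planned 338 remains sufficient on its own assumptions.

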#### Hypotheses on health professionals

Patients are more likely to receive recommended CVRM and reach CVRM targets in general practices which have social networks characterized by: high density, high frequency of contact, high homogeneity, an appointed CVRM-coordinator who has a high degree of centrality, and a consistently identified opinion leader for CVRM.

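### The professional-performance regressions make no provision for clustering by practice, although their main predictors are practice-level; fitted to patient records as written, they would give standard errors that are too small

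*Protocol article*

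**What the plan says.** All references are to the protocol article.

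- **Model.** Under Statistical analyses, for the hypothesis tests: "we will use multivariate logistic regression models to investigate the effect of social networks characteristics on professional performance of practice nurses". Six network characteristics are the predictors of main interest. The controls are trial arm, personal characteristics of the professional, and practice characteristics. For patients' self-management and health outcomes, "several multivariate logistic regression models will be estimated". Change is analysed by similar models with the baseline value added, and by ordinal logistic regression in three categories.
- **Level of the hypothesis.** Hypotheses on health professionals: "Patients are more likely to receive recommended CVRM and reach CVRM targets in general practices which have social networks characterized by", followed by density, contact frequency, homogeneity, a central coordinator and a consistently named opinion leader. Construction of network characteristics defines density and centrality as features of a whole network.
- **Level of the outcome.** Health care professionals and their alters defines professional performance as adequate or inadequate according to what is recorded in the individual patient's file.
- **Data structure.** Sample size calculation says the host trial is sized "by including 900 patients clustered within 30 practices". Sample says: "Per practice we plan to include 15 patients with established CVD and 15 at high risk".

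The only mention of clustering is in the sizing of the host trial. The random permutation tests under Statistical analyses are for comparing network characteristics, not for these regressions.

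**The concern.** Every patient in a practice shares the same network density, homogeneity and centralisation, the same coordinator and opinion-leader status, the same practice size, and the same trial arm if arms were allocated by practice. For such predictors the independent information comes from 30 practices. A logistic model that treats 900 records as independent gives standard errors that are too small whenever patients in one practice resemble each other in the care they receive.

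These regressions are the tests of the key hypotheses and serve the second and third research aims. The Discussion suggests that the results could inform how care teams are composed. Between-practice noise reported as a network effect would therefore mislead in exactly the use the authors foresee.

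**Working it through.** **The plan's own figure.** The article gives no sample size or precision figure for the network regressions. Its one calculation concerns invitation response rates: "Assuming alpha is 0.05, power of 0.80, a response rate of 50% in the first group and 65% in the second group", from which "we estimated that we need to include 338 patients". With a two-sided test and no continuity correction, n per group = [1.96·√(2 × 0.575 × 0.425) + 0.842·√(0.50 × 0.50 + 0.65 × 0.35)]² / 0.15² ≈ 169.3. That is 170 per group and 340 in total; power at 169 per group is 0.799. The stated figure reproduces to within two patients and is not affected by this point.

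**Inputs for the regressions.**
- 900 patients and 30 practices (Sample size calculation).
- 15 + 15 = 30 patients per practice (Sample).
- ICC: not given, so a range is assumed.

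**Formulas for a predictor that is constant within practice.**
- Design effect: DE = 1 + (30 − 1) × ICC.
- Effective sample size: 900 / DE.
- The single-level standard error is too small by a factor √DE.
- True type I error of a nominal two-sided 5% test: 2 × [1 − Φ(1.96 / √DE)].

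| Assumed ICC | DE | Effective N | √DE | Type I error |
|---|---|---|---|---|
| 0 | 1.00 | 900 | 1.00 | 5.0% |
| 0.01 | 1.29 | 698 | 1.14 | 8.4% |
| 0.02 | 1.58 | 570 | 1.26 | 11.9% |
| 0.05 | 2.45 | 367 | 1.57 | 21.1% |
| 0.10 | 3.90 | 231 | 1.97 | 32.1% |

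The error passes 10% at an ICC of about 0.015, 15% at about 0.029 and 20% at about 0.046.

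**Simulation check.** Each setting used 2000 runs of 30 practices × 30 patients. The outcome was beta-binomial with mean 50% or 30%, and the logistic model contained trial arm plus one or six null practice-level predictors. Rejection rates were about 8–9%, 11–13%, 20–22% and 31–34% at ICC 0.01, 0.02, 0.05 and 0.10. A practice-level linear regression on the same data, extended to ICC 0 and 0.20, stayed at 4.4% to 5.6%. With six null predictors, the chance of at least one false positive was about 25% without clustering and about 73% at ICC 0.05.

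**Indirect anchor for the ICC.** The host trial is "powered to detect a 15% difference in provided personalized lifestyle advice". Assume alpha 0.05, power 0.80, a control rate of 35% to 50% and no allowance for dropout. An individually randomised trial would then need 340 to 348 patients. The planned 900 imply DE of 900/348 = 2.59 to 900/340 = 2.65, so an ICC of about 0.055 to 0.057. The assumptions are not in the article, so this shows only that 0.05 is not far-fetched.

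**Patient-network predictors.** These vary between patients within a practice, so the design effect is about 1 + 29 × ICC(predictor) × ICC(outcome). With both at 0.05: 1 + 29 × 0.0025 = 1.07, type I error about 5.8%. With both at 0.10: 1 + 29 × 0.01 = 1.29, about 8.4%.

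**The case against.** The best defence is that this is a condensed article and the wording does not exclude a multilevel version. A reader might infer that the plan prescribes ordinary single-level regression on 900 patients. The text does not say so. It never uses the word ordinary and does not state the unit of the performance model, whose controls are all provider or practice variables apart from trial arm. If performance were aggregated to nurse or practice, the figures above would not apply. That part of the defence stands.

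It does not remove the point. The article gives the model family, the predictors, the controls, both approaches to change, the ordinal categories and the software. In that much detail, a model with no practice term is a stated method that does not fit the stated design.

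A reader might also infer that false positives will run at several times 5%. That depends on an ICC the article does not give: the ratio is 1.7 at ICC 0.01, 2.4 at 0.02, 4.2 at 0.05 and 6.4 at 0.10. The relevant value is the residual ICC after adjustment for arm and practice characteristics, which may be lower than the raw one. Nor does the inflation carry over to the patient-network models at the same size.

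Finally, the aims are exploratory. This lowers the stakes somewhat, but the same section describes the models as tests of the hypotheses, and an exploratory estimate still needs a valid standard error.

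**Conclusion.** The point holds in conditional form. The logistic and ordinal models make no provision for practice, while the professional-network predictors are mainly practice-level and the outcome is scored per patient record. If the performance models are fitted to those records as written, the nominal 5% test of a practice-level predictor has a true error of about 8% to 32% over assumed ICCs of 0.01 to 0.10, with 30 patients per practice. The patient-network models are only mildly affected, at about 6% to 8% with both ICCs at 0.05 to 0.10. The ordinal change models share the omission, but their inflation was not simulated. That the authors in fact intend to ignore clustering is not established.

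**What to change.** State the unit of analysis for the professional-performance models. Then account for practice in both the logistic and the ordinal models, by a random practice intercept or by GEE with a small-sample correction for 30 clusters. Alternatively, analyse the practice-level predictors at practice level. The same provision should cover the patient-network models for consistency, though it will change little there.

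The cost is a short change of wording, slightly more analysis work in R, which the article already names, and wider intervals for the professional-network effects. No new data are needed.

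One practical limit should be acknowledged. Six network characteristics plus arm, practice size and project involvement make nine terms, which leaves 30 − 9 − 1 = 20 residual degrees of freedom at practice level. Precision will be limited and the full model may be hard to fit. This is not a reason to drop the confounders the plan specifies.
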